### Cost-effectiveness evaluation

An economic analysis of Copen-SCALE will be conducted to inform decision makers about the costs and benefits of implementing Copen-SCALE. Two types of economic evaluation (i.e., cost-effectiveness and cost-benefit analysis) will be performed, both from employers’ perspective. All analyses will be based on data collected between baseline and 6–8 month follow-up, according to the intention-to-treat principle with multiple imputation of missing data [39].

## Data collection for the economic evaluation

### Health-related productivity loss costs

Absenteeism (days missed from work due to sickness absence) will be measured from workplace registers.

Presenteeism (reduced performance related to health problems while being present at work) will be measured by a small electronic questionnaire for employees at baseline and follow up [30, 31]. Absenteeism and presenteeism costs will be estimated using the Human Capital Approach, because this method assumes that the salary of an employee equals the productivity loss of that employee. As a result, health-related productivity losses (i.e., both presenteeism and absenteeism) will be valued using average gross salaries in the municipality depending on personnel category. To assess the robustness of the Human Capital approach we will supplement with a Friction-Cost approach.

### Intervention costs

We consider the following costs for implementing the intervention:Staff time: Employees’ and managers’ participation in intervention activities (registration of participation in activities that are not directly part of daily work (e.g., a workshop/meeting for planning the activities). Employees’ and managers’ costs will subsequently be valued based on their average gross salaries in the municipality, including overhead costs.Consultants’ time: The time spent on implementing the intervention by the consultants will be registered. Their costs will be based on their usual consultancy fees.Consumables: Materials cost, i.e., exercise bands and activity cards, will be assessed using invoices.Overhead: We incorporate an overhead cost of 20% of the intervention (such as the cost of booking the meeting rooms, telephone bills, catering, electronics usage).

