### Cost-benefit analysis

In a cost-benefit analysis, we will calculate the net benefit of the intervention, expressed as Return On Investment (ROI) and Benefit to Cost Ratio (BCR). The costs comprise all the relevant expenses for the intervention, detailed above. The benefits comprise the monetary gain due to a change in absenteeism and presentism. Further, to arrive at a conservative estimate we will also conduct a separate cost-benefit analysis using only the change in sickness days, absenteeism, reported by institutions and/or the municipality. To simulate potential incremental cost-benefit gained in the years after the intervention we will simulate two scenarios. In the first, we assume a constant effect of the intervention over time. In the second scenario, we assume a fade-out effect in which the effect fades-out over a 5-year period with a constant rate.

To supplement the cost-benefit analysis, we perform a cost-effectiveness analysis considering also changes in experienced pain. The costs are calculated as intervention costs minus sickness-related costs. The effects comprise musculoskeletal pain changes, using questionnaire data on average pain over the last seven days, viewed as an interval scale. The 95% confidence intervals for the ICERs will be estimated using the bootstrapping method (one thousand bootstrap samples with replacement) (71). The bootstrapped incremental cost and effect pairs will be graphically presented on cost-effectiveness planes (72). Cost-effectiveness acceptability curves will be estimated to assess the probability of the intervention being cost-effective as a function of the employer’s willingness to pay.

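### On a plain reading, a staff hour is priced with overhead when spent on the intervention and without it when saved from absence or presenteeism, and both prices enter the same ROI, BCR and net cost

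*Protocol article*

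**What the plan says.** Under Intervention costs, the time of employees and managers "will subsequently be valued based on their average gross salaries in the municipality, including overhead costs". Consultants are costed separately: "Their costs will be based on their usual consultancy fees". A further line reads "We incorporate an overhead cost of 20% of the intervention", with examples: "such as the cost of booking the meeting rooms, telephone bills, catering, electronics usage". Neither the salary overhead rate nor the base of the 20% is given.

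Under Health-related productivity loss costs, absenteeism and presenteeism "will be valued using average gross salaries in the municipality depending on personnel category". The Human Capital Approach is chosen because "this method assumes that the salary of an employee equals the productivity loss of that employee". Overhead is not mentioned there.

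The Cost-benefit analysis section brings the two together. On the cost side, "The costs comprise all the relevant expenses for the intervention, detailed above". The benefit side is the money gained from changes in absenteeism and presenteeism. The supplementary cost-effectiveness analysis in that section subtracts sickness-related costs from intervention costs. The Cost-effectiveness evaluation section gives the employer's perspective for both types of economic evaluation.

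**The concern.** The two valuation rules share the same base, average municipal gross salary, but only the cost-side rule adds overhead. An hour that a worker spends in a workshop outside daily work and an hour that the same worker is absent are both paid hours lost to the same employer. The perspective is the same throughout, so it cannot explain two prices.

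If the rules are applied as printed, ROI and BCR divide hours valued at one rate by hours valued at another, and the net cost subtracts one from the other. These results are meant to tell decision makers whether the programme pays for itself. Near break-even, the choice of hourly rate could decide the sign of the ROI.

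**Working it through.** The article states no ROI, overhead rate or cost split for this trial, so there is no figure of its own to reproduce. The 63% ROI in the Background belongs to the earlier TOY trial, and its inputs are not shown. It serves here only as an illustrative starting value.

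**Inputs**
- 20% overhead line: Intervention costs, taken here on the whole intervention.
- h, overhead on staff salary: not given; assumed 10-30%.
- s, staff share of intervention cost at plain gross salary: not given; assumed 30-70%.

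**As written.** Set the intervention cost at plain gross salary, before the 20% line, to 1. Then

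C = 1.2 × [s(1+h) + (1−s)] = 1.2 × (1 + s·h).

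The benefit B is priced at plain gross salary, BCR = B/C and ROI = B/C − 1. The ratio of the price of an hour spent to an hour saved is 1+h, that is 1.10 to 1.30.

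**Alternative A: overhead on both sides.** B becomes B(1+h) and C is unchanged, so

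1 + ROI(A) = (1 + ROI) × (1+h). The staff share drops out.

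**Alternative B: salary overhead on neither side, 20% line kept.** C becomes 1.2 and B is unchanged, so

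1 + ROI(B) = (1 + ROI) × (1 + s·h). The factor 1.2 cancels. The product s·h runs from 0.3 × 0.10 = 0.03 to 0.7 × 0.30 = 0.21.

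**Results**

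| ROI as written | A: overhead on both sides | B: salary overhead on neither |
|---|---|---|
| 63% | 1.63 × 1.10 to 1.63 × 1.30: 79% to 112% | 1.63 × 1.03 to 1.63 × 1.21: 68% to 97% |
| 0% | +10% to +30% | +3% to +21% |
| −20% | 0.80 × 1.10 to 0.80 × 1.30: −12% to +4% | 0.80 × 1.03 to 0.80 × 1.21: −18% to −3% |
| −130% (absence or presenteeism worsens) | −0.30 × 1.10 to −0.30 × 1.30: −133% to −139% | −0.30 × 1.03 to −0.30 × 1.21: −131% to −136% |

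In the first three rows the benefit is positive and the ROI as written is too low. In the last row the benefit is negative and the ROI as written is too high, because the extra hours lost are priced too cheaply relative to hours spent. A and B are two ways to remove one mismatch. Applying both would create the opposite mismatch.

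**The case against.** The strongest reply is that the unequal price is inferred from silence. The productivity-loss section does not exclude overhead, and an article condenses a longer protocol. The words about overhead in the staff-time rule may also simply anticipate the 20% line. On that reading a staff hour has one price, plain gross salary, and the bias is zero. This possibility stands and limits how firmly the point can be put. It does not remove the point. Both rules are printed, overhead is written into one and left out of the other, and the justification given for the second is that salary itself measures the loss. The friction-cost supplement and the analysis restricted to absenteeism do not help, since neither brings the rate for intervention hours into line with the rate for hours saved.

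Three stronger readings are tempting, and the article does not support them.

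- **Overhead is charged twice.** A reader might multiply the two overheads and say that a workshop hour costs 1.2 × (1+h) = 1.32 to 1.56 times an absence hour. But the examples for the 20% line are rooms, telephone, catering and electronics. These are non-salary items with no other cost line. The two would overlap only if they cover the same things or if the 20% is taken on a base that already carries overhead, and the text does not settle that.
- **ROI is always biased downward.** That needs h above zero and a positive benefit. The last row of the table shows the reverse.
- **The cost-side and benefit-side effects add up.** They are alternative corrections of the same mismatch.

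**Conclusion.** The point holds in limited form. On the plain reading, the plan gives an hour of the same worker two prices, in the ratio 1+h, and combines them in one employer-perspective ROI, BCR and net cost. If time is saved, ROI and BCR come out too low. With h = 10-30% and s = 30-70%, both assumed, an illustrative 63% would be 79-112% with overhead on both sides or 68-97% with salary overhead on neither. From −20%, putting overhead on both sides gives −12% to +4%, so the sign can change. The true size cannot be derived from the article, and it is zero if the overhead wording only refers to the 20% line. Double charging of overhead is not shown.

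**What to change.** 1. Use one hourly rate per personnel category for both intervention time and absence or presenteeism time, and state whether that rate includes salary overhead and at what percentage.
2. Keep the 20% line for the non-salary items that it lists. State the base on which it is taken, so that it does not repeat salary overhead or any overhead already inside the consultancy fees.
3. Report ROI and BCR under the alternative convention (overhead on both sides, or salary overhead on neither) as a sensitivity analysis.

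This takes a few sentences and one extra calculation, with no new data.

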### Cost-effectiveness analysis

The total employer’s costs of the intervention will be estimated and compared between the intervention and control group. The incremental cost-effectiveness ratio (ICER) will be calculated by dividing the mean difference in costs (incremental cost) between both groups by the difference in effects (incremental effect) on the outcome measures, i.e., pain-related sickness absence and musculoskeletal pain. The 95% confidence intervals for the ICERs will be estimated using the bootstrapping method (1000 bootstrap samples with replacement) [41]. The bootstrapped incremental cost and effect pairs will be graphically presented on cost-effectiveness planes [42]. Cost-effectiveness acceptability curves will be estimated for the probability that the intervention will be more cost-effective than usual practice as a function of the employer’s willingness to pay.

### Cost-benefit analysis

In a cost-benefit analysis, we will calculate the net benefit of the intervention, expressed as Return On Investment (ROI) and Benefit to Cost Ratio (BCR). The costs comprise all the relevant expenses for the intervention, detailed above. The benefits comprise the monetary gain due to a change in absenteeism and presentism. Further, to arrive at a conservative estimate we will also conduct a separate cost-benefit analysis using only the change in sickness days, absenteeism, reported by institutions and/or the municipality. To simulate potential incremental cost-benefit gained in the years after the intervention we will simulate two scenarios. In the first, we assume a constant effect of the intervention over time. In the second scenario, we assume a fade-out effect in which the effect fades-out over a 5-year period with a constant rate.

To supplement the cost-benefit analysis, we perform a cost-effectiveness analysis considering also changes in experienced pain. The costs are calculated as intervention costs minus sickness-related costs. The effects comprise musculoskeletal pain changes, using questionnaire data on average pain over the last seven days, viewed as an interval scale. The 95% confidence intervals for the ICERs will be estimated using the bootstrapping method (one thousand bootstrap samples with replacement) (71). The bootstrapped incremental cost and effect pairs will be graphically presented on cost-effectiveness planes (72). Cost-effectiveness acceptability curves will be estimated to assess the probability of the intervention being cost-effective as a function of the employer’s willingness to pay.

### Implementation evaluation

We will employ the taxonomy of implementation outcomes outlined by Proctor et al. (2011) - Implementation Outcomes Framework (IOF) [29]. Implementation will be evaluated through the outcomes of acceptability, adoption, appropriateness, feasibility, fidelity, implementation cost, penetration, and sustainability, each representing a distinct dimension of the implementation process (Table 1).

**Table 1 Tab1:** Implementation outcomes: inspiration from Guerin et al. 2022 [44] which will be used to evaluate how and to what extent Copen-SCALE has been implemented across the participating childcare institutions across Copenhagen municipality

Outcome	Definition	Measure or scale
PRIMARY IMPLEMENTATION OUTCOME		
Fidelity	*Degree to which the intervention is implemented as intended by the consultants.*	-Interventions logs filled in by the consultants - Observations of intervention activities
SECONDARY IMPLEMENTATION OUTCOMES		
Acceptability	*The perception among childcare institutions that the intervention is agreeable and satisfactory.*	- Questionnaire: Acceptability of Intervention Measure (AIM) [43]
Adoption	*Intention among childcare institutions to employ the intervention (i.e.*,* “uptake”).*	- Recruitment data on workplace settings and characteristics
Appropriateness	*Perceived fit of the intervention for childcare institutions*	-Questionnaire: Intervention Appropriateness Measure (IAM) [43]
Costs	*Directly measured non-research costs*,* including all costs of implementation*	-Register of costs involved in implementing of the intervention
Feasibility	*Extent to which the intervention can be successfully applied to the childcare institutions*	-Questionnaire: Feasibility of Intervention Measure (FIM) [43]
Penetration	*Extent of integration of Copen-SCALE in the childcare institutions*	-Interviews
Sustainability	*Extent to which the intervention is maintained or institutionalized within the childcare institutions*	-Interviews

### Data collection

We will conduct a mixed method, multi-dimensional evaluation of the implementation of the Copen-SCALE. The evaluation will combine recruitment data, interviews, observations, and questionnaires. Table 1 outlines the implementation outcomes, their definitions and the assessment measure or scale.

### Primary implementation outcome - fidelity assessment

The fidelity assessment is inspired by the framework developed by Ferm et al. that suggests that fidelity includes information about the content of the intervention (success criteria), and quality of the intervention [45]. Questions about success criteria for specific activities in the Copen-SCALE intervention will be generated (see Table 2). After each activity, consultants will complete an intervention log containing two types of assessments:

**Table 2 Tab2:** The fidelity questions that will be used to assess if the Copen-SCALE was successfully delivered as intended. These questions will be included in the intervention log that consultants will complete after each intervention activity is conducted. The consultants’ answers to these questions will be converted into a score from 0-100, where 100 indicates 100% fidelity [45]

PRIMARY INTERVENTION OUTCOME: FIDELITY	
Outcome	Measure
Content (success criteria)	Have you implemented the following according to the manual: [# success criteria]? Response: [“not implemented,” “partly implemented,” “completely implemented”, and “implemented more in depth.”]
Quality (Contribution to the participants’ learning)	Regarding today, to which extent have you contributed to… …the participants’ commitment and motivation? …ensuring the employees’ participation in the activity? …adapting the activity to the needs of the participants? …maintaining the participants’ attention? Response: [to a very large extent/to a large extent/some-what/to a small extent/to a very small extent]
Quality (Self-rated performance)	Suppose that your performance, at its best, is equal to 10 points. How would you rate your performance today?

Quality of Performance: Consultants will use a Likert scale to rate their own performance, with the prompt: “Imagine your performance can be worth ten points at its best. To what extent have you today contributed to engaging employees, ensuring their participation, adapting the program, or maintaining focus?” The score will later be converted to a scale from 0 to 100.

Content Fidelity: A yes/no scale will be used to evaluate whether the activity adhered to the protocol. If the response is “no,” consultants will have the opportunity to provide additional details explaining the deviation. Simple T-test analyses will be used to assess differences between the workplaces. Moreover, the research team will conduct random observations at the workplaces to further assess the fidelity of the intervention activities. An observation protocol will be developed to capture various aspects of the intervention activities, including information about content, quality, and contextual factors. The data gathered through this protocol will complement the information recorded in the consultants’ intervention logs, offering a more comprehensive understanding of the fidelity and contextual factors influencing the intervention’s implementation.

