### Setting and participants

All 350 childcare institutions in the municipality of Copenhagen are invited to be enrolled in Copen-SCALE. All childcare workers (~ 7.200) [21] in the 350 childcare institutions will be eligible for participation in the evaluation. Copen-SCALE is planned to have a duration of 4 years, including up to eighty-seven childcare institutions per year, beginning in January 2024 and ending ultimo 2027.

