### The intervention

Copen-SCALE consists of four evidence-based areas of intervention: (1) children’s self-reliance and motor skills, (2) ergonomics, (3) education in prevention and handling pain, and (4) health-promoting physical activity. The intervention involves a structured 3-hour workshop with employees during working hours, cf. Figure 1. This workshop focuses on educating childcare workers about the intervention components while also encouraging them to identify specific work-related challenges they wish to address. Additionally, participants develop actionable plans to improve their work situations. Following the workshop, the intervention includes 2 to 3 visits by a consultant at the workplaces. During these visits, the consultant provides ongoing support and monitors the implementation of the intervention to ensure its effectiveness and sustainability.

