### Sample size

It is important to consider statistical power when designing an implementation study. As implementation research is aimed at system-level changes, the power of a given study depends on working units (e.g., childcare institutions) as opposed to individual employees. Therefore, traditional methods of sample size and power calculation are usually not applicable as they fail to consider clustering and the extended time-frames of implementation studies [26]. To address this complexity, we utilize a recommended tool, the Optimal Design with Empirical Information (OD+), for effectively planning and powering these complex study designs [27]. Considering a power of 80%, an alpha level of 0.05, and a reliability of 0.70, the required sample size for our study is determined to be seventy-four childcare institutions. Given that we have up to 350 eligible childcare institutions for participation, we believe that we will be able to fulfill the targeted number in our sample size calculation.

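### Simple t-tests cannot show how fidelity varies among 74 to 350 workplaces, and the article names neither two groups to compare nor a unit of analysis

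*Protocol article*

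**What the plan says.** Table 1 and the section on the fidelity assessment make fidelity the lead implementation outcome. The data come from the people who deliver the programme: "After each activity, consultants will complete an intervention log". Table 2 converts their answers to a score from 0 to 100, and part of that score is the consultant's rating of his or her own performance.

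Under The intervention, each workplace has one workshop, after which "the intervention includes 2 to 3 visits by a consultant at the workplaces". The number of workplaces is bounded by two statements. Under Setting and participants, "All 350 childcare institutions in the municipality of Copenhagen are invited to be enrolled in Copen-SCALE", with a yearly intake of at most 87. Under Sample size, "the required sample size for our study is determined to be seventy-four childcare institutions".

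The only inferential statement for fidelity is "Simple T-test analyses will be used to assess differences between the workplaces". The article does not say which two groups are compared, whether the unit is the log or the workplace, or how several comparisons would be handled. Multilevel modelling appears only under Effectiveness analysis.

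The t-test sentence sits in the paragraph on content fidelity, which describes a yes/no answer. Table 2 gives four response levels for content.

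**The concern.** The stated method does not match the stated question. A two-sample t-test contrasts two means of independent observations, whereas the question is how a score differs across many workplaces, each seen a few times by a rater who also delivered the activity. Three features of the data have no place in a simple t-test:

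- the number of workplaces, far above two;
- several logs per workplace, from a workshop and from visits, which need not score alike;
- the rater, whose leniency may differ from that of other raters.

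At stake is whether the analysis can separate workplaces where delivery fell short from consultants who mark themselves strictly. The effectiveness analysis is not touched. This is a method the article commits to, so an analysis plan that followed the sentence would carry the mismatch forward.

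**Working it through.** The article gives no error rate, power or sample size for the fidelity comparison, so there is no figure to reproduce. The steps below show what each reading of the sentence would imply.

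**Inputs from the article.** Workplaces k: 74 (Sample size), 87 per year and 350 in total (Setting and participants). Logs per workplace: 1 workshop + 2 to 3 visits = 3 to 4. The 0.05 level is stated for the sample size only; its use for fidelity, two-sided, is an assumption.

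**Reading 1: every pair of workplaces, uncorrected.** Tests = k(k − 1)/2. Expected false positives if all workplaces are equal = tests × 0.05.

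| k | Tests | Expected false positives |
|---|---|---|
| 74 | 74 × 73/2 = 2,701 | 135.05 |
| 87 | 87 × 86/2 = 3,741 | 187.05 |
| 350 | 350 × 349/2 = 61,075 | 3,053.75 |

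The pairs share workplaces and so are not independent, but the expected counts do not need independence. Each test would have only 3 + 3 − 2 = 4 to 4 + 4 − 2 = 6 degrees of freedom. A Bonferroni level for 350 workplaces would be 0.05/61,075 = 8.2 × 10⁻⁷.

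In a pairwise test the logs are the replicates, so having several per workplace is not in itself an error. Extra inflation comes from the rater. Simulated type I error of one pairwise test, with no true workplace difference and an assumed consultant intraclass correlation (ICC):

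| Consultant ICC (assumed) | Different consultants, 3 logs | Different consultants, 4 logs |
|---|---|---|
| 0 | 4.9% | 4.8% |
| 0.1 | 7.1% | 8.8% |
| 0.3 | 13.8% | 18.7% |
| 0.5 | 24.0% | 31.2% |

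When the same consultant rates both workplaces, the rate stays near 5%.

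**Reading 2: two groups of workplaces.** Simulated type I error with 4 logs per workplace and 10 consultants (assumed). The ICCs for consultant and for workplace are assumed equal, at 0.1 each or 0.2 each:

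| Workplaces | ICC each | Logs pooled, consultants in both groups | Workplace means, consultants in both groups | Logs pooled, consultants in one group only | Workplace means, consultants in one group only |
|---|---|---|---|---|---|
| 74 | 0.1 | 11.5% | 5.1% | 35.5% | 26.1% |
| 74 | 0.2 | 19.4% | 5.4% | 49.3% | 33.2% |
| 350 | 0.1 | 12.2% | 5.5% | 61.7% | 53.1% |
| 350 | 0.2 | 18.3% | 5.2% | 72.8% | 59.3% |

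The pooled-log inflation does not need a consultant effect. With consultant ICC 0 and workplace ICC 0.3, pooling logs gives 15.5% (74 workplaces) and 14.1% (350), against 5.6% for workplace means in both cases. The design effect agrees: 1 + (4 − 1) × 0.3 = 1.9, and 2[1 − Φ(1.96/√1.9)] = 15.5%.

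**What follows.** The nominal rate is kept in two settings: two defined groups compared on workplace means with consultants spread over both, or a single pair rated by one consultant. The article specifies neither.

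**The case against.** The strongest reply is that the sentence need not mean pairwise testing. The article offers natural two-level contrasts, such as nursery against pre-school, public against private, or spring against autumn start. On workplace means, with consultants working in both groups, a t-test is legitimate and holds its level. An article may leave the choice of groups and unit to a fuller document. Fidelity is also largely a descriptive question, and the researchers' own observations supplement the logs.

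Much of this stands as a limit on the size of the problem. A reader might infer that the plan will generate thousands of false positives. The article does not support that: it announces no pairwise testing and no significance level for fidelity. A reader might also add the pairwise counts to the repeated-log problem, but these belong to different readings. Nor does the article say that consultants each rate many workplaces. It says under Implementation strategies only that they come from one consultancy, without their number or allocation.

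What does not stand is the rescue of the sentence. The safe reading needs named groups, workplace means and a suitable consultant allocation, and none of these is stated. Observations by the research team enrich the evidence but do not change the test applied to the scores.

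**Conclusion.** The point holds as a mismatch between a stated method and its question. With 74 to 350 workplaces, a test of two means cannot quantify variation in fidelity between workplaces, and it cannot separate workplace from rater.

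The size is conditional. The range of 135 to 3,054 expected false positives applies only to uncorrected testing of all pairs at 0.05 with all workplaces equal. The inflation from pooled logs or from consultants rests on assumed ICCs and, for the two-group figures, on 10 assumed consultants; the article gives no value for either. Under one two-group reading there is no material inflation. The change should be made because it concerns the primary implementation outcome and costs little. The primary effectiveness outcome is unaffected.

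**What to change.** Replace the t-test sentence with one linear mixed model of the 0-100 fidelity score:

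- fixed effects for activity type (workshop or visit) and calendar time;
- random intercepts for workplace and for consultant;
- between-workplace and between-consultant variances reported with intervals;
- any systematic difference of interest, such as nursery against pre-school, entered as a named covariate.

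The two variances can be separated only if consultants serve more than one workplace, so the allocation should be described. With few consultants the consultant variance will be imprecise, and its interval will show this.

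If a two-group comparison is what is meant, name the groups and compare workplace means with a consultant effect. Workplace means alone are not enough if consultants are confined to one group.

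Before either, reconcile the yes/no content answer in the text with the four levels in Table 2, and state how the answers become the 0-100 score. If content is binary, a linear model or t-test of single logs may not suit it.

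The cost is a sentence or two, slightly more analysis work in standard software, and workplace and consultant identifiers in every log.
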